### Treatment strategies

#### Intervention group

The intervention group receives a prescription for sociotherapy as a component of the structured DM.

#### Control group

The control group receives standard care, which includes regular DM following psychiatric treatment but does not involve a prescription for sociotherapy.

### Assignment procedures

To address potential confounding in the observational data we estimate propensity scores based on the probability of receiving sociotherapy. These scores will be calculated using logistic regression controlling for key characteristics of the index event, other prescribed DM measures, medical history and sociodemographic characteristics (for a detailed description see Table 2). Afterwards the propensity scores will be applied by either propensity score matching (PSM) or inverse probability weighting (IPW) depending on the distribution of the scores. Balance diagnostics such as standardized mean differences will be conducted and all steps of the procedure including the applied methods will be reported.

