### Sample size calculation

The required sample size for thetarget trial was determined based on the primary outcome of interest: the 30-day hospital readmission rate. To achieve sufficient statistical power (80%) to detect a minimal clinically relevant difference in the 30-day readmission rates (effect size = 0.3) between participants receiving sociotherapy and those receiving standard care, we conducted a priori power calculations (Appendix 1). Since the required sample size depends not only on the effect size but also on the outcome rate in the non-exposed group– a figure currently unknown– we calculated a range of sample sizes across plausible outcome rates [10]. Assumingan effect size of 0.3, the necessary sample size is N = 449 when the baseline readmission rate is 10%, and decreases to N = 329 when the baseline rate increases to 20%. If the required sample size based on the outcome rate in the non-exposed group (see Assignment Procedure) is not reached in our dataset, the TTE will be discontinued, and the journal will be notified. A detailed explanation outlining the reasons for the termination will be provided to ensure transparency and maintain the integrity of the study’s reporting. Exploratory analysis may be conducted.

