### Trial emulation

#### Data

This study is based on insurance claims data of the German Techniker Krankenkasse (TK). TK is a German statutory health care insurance provider with a market share of approximately 15.3%. In the present study, we will use TK claims data for the years 2021 to 2024 of each individual fulfilling the eligibility criteria in 2022 to 2023 [11].

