#### Eligibility criteria

The inclusion criteria for the study require participants to have received at least one psychiatric or psychosomatic treatment^1^ in an inpatient, semi-inpatient, or inpatient equivalent setting between January 2022 to December 2023, under the Psychiatric and Psychosomatic Compensation System (German Akronym: PEPP). In a PEPP number, the first two positions define the structural category, while the subsequent positions offer further specification. Included PEPP structural categories are PO (particularly complex cases), PP (psychosomatics), and PA (psychiatry) for inpatient treatment. For semi-inpatient and inpatient equivalent treatments, the relevant categories are TP and QA (both psychiatry). Not included are the categories for child and youth psychiatry and psychotherapy (codes PK, TK, and QK), in each care setting. Additionally, participants must have reached the age of 18 by the time of the index event. Since a structured DM is required by law we do not include it as an inclusion criterion.

The exclusion criteria for the study are: a previous inpatient or outpatient prescription of sociotherapy within 365 days before the last day of the index event. Additionally, we will exclude individuals who did not maintain continuous insurance coverage throughout the study period including baseline and follow-up period (January 2021– December 2024); employees of TK; individuals who have a registered data protection notice; and those who have explicitly objected to the use of their healthcare records for research purposes.

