### Analyses of primary and secondary outcomes

The primary outcome will be analyzed with logistic regression models to evaluate the association between sociotherapy and the 30-day readmission rate. This model will be adjusted for potential confounders as described below. Both ITT and PPA will use the same statistical models for the analysis. However, since the magnitude of the odds ratios estimated in logistic regression model cannot be compared across models, we can only compare whether the effects are positive or negative [12, 13].

For the secondary outcome 365-day readmission to psychiatric hospitalization, we will apply the same procedure as for the primary outcome 30-day readmission. Regarding time to first psychiatric readmission, we will generate cumulative incidence curves to illustrate the time to readmission for participants in both the intervention and control group. The log-rank test will be employed to compare the distributions. Further, we will use Cox-regression models to account for confounders. The secondary outcome total number of psychiatric hospitalizations within a 365-day period and cumulative number of days spent in the hospital due to psychiatric admissions we will apply Poisson regression models. In cases where overdispersion is detected, we will instead use negative binomial regression models. If a high prevalence of zero counts is observed, we will address this by applying zero-inflated Poisson or zero-inflated negative binomial regression models. Both ITT and PPA will be applied to all secondary outcomes.

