### Confounders

In all multivariate analyses, we will adjust for key characteristics of the index event, including the PEPP category, the length of the index event, diagnoses of index event (dementia, substance abuse, schizophrenia and schizoaffective disorder, bipolar disorder and manic episodes, major depressive disorder, post-traumatic stress disorder, and personality disorder), the necessity for intensive treatment (OPS-Code 9–61), whether the admission was an emergency admission, other prescribed or certified DM measures (medication, remedies and aids, home care, outpatient intensive care specialized outpatient palliative care, patient transportation, digital health applications, and incapacity certificate). We will also control for participants' medical history prior to the index hospitalization, as such previous psychiatric hospitalizations, comorbidities in form of the Elixhauser Comorbidity Index [14] and care level. As for demographic variables, we will include age, sex, population density at the place of residence and the German Index of Socioeconomic Deprivation [15] (Table 2).

**Table 2 Tab2:** Variables

Category	Variable	Operationalization
Exposure	Sociotherapy	Prescription of Sociotherapy as a DM measure (ITT) / Prescription of Sociotherapy as a DM and utilization of at least one sociotherapy session (PPA)
Index event	PEPP	PO/PP/PA/TP/QA
	Length of index event	Number of days of index event
	Dementia	F00.x– F03.x, G30.x
	Substance abuse	F10.2, F11.2, F12.2, F13.2, F14.2, F15.2, F16.2, F17.2, F18.2, F19.2
	Schizophrenia & Schizoaffective disorder	F20.x, F21.x; F25.x
	Bipolar disorder & Manic episodes	F30.1– F30.2, F31.1– F31.2, F31.4- F31.6
	Major depressive disorder	F32.2– F32.3; F33.2– F33.3
	Post-traumatic stress disorder	F43.1
	Personality disorder	F60.x– F61.x
	Intensive treatment	OPS 9–61
	Emergency admission	Reason for admission
Discharge management measures (presciptions and certificates)	Medication	
	Remedies and aids	
	Home care	
	Outpatient intensive care	
	Specialized outpatient palliative care	
	Patient transportation	
	Digital health applications	
	Incapacity certificate	
Medical history	Elixhauser Comorbidity Index [16]	Based on all available diagnoses twelve months prior to the index event
	Number of psychiatric hospital days	Hospital stays with PEPP categories PO, PP, PA, TP & QA based on all available data twelve months prior to the index event
	Care level	Based on care level on the last day prior to the index event

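### Two years of discharges are pooled with no calendar-time term in the propensity score or the outcome models, which leaves a modest and avoidable route to confounding

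*Protocol article*

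**What the plan says.** The Data section of the protocol article states that "we will use TK claims data for the years 2021 to 2024 of each individual fulfilling the eligibility criteria in 2022 to 2023", and the Eligibility criteria section takes index treatments "between January 2022 to December 2023, under the Psychiatric and Psychosomatic Compensation System". All index events in those 24 months form one study population.

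Under Assignment procedures, "These scores will be calculated using logistic regression controlling for key characteristics of the index event, other prescribed DM measures, medical history and sociodemographic characteristics", with Table 2 named as the detailed description. The scores are then used for matching or for inverse probability weighting.

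The Confounders section applies the same set to the outcome models: "In all multivariate analyses, we will adjust for key characteristics of the index event, including the PEPP category, the length of the index event". It goes on through diagnoses, intensive treatment, emergency admission, other discharge measures and medical history, and ends with "As for demographic variables, we will include age, sex, population density at the place of residence and the German Index of Socioeconomic Deprivation". The primary analysis takes over that list: "This model will be adjusted for potential confounders as described below".

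Neither the text nor Table 2 lists a date, quarter or year of discharge. No matching or stratification on calendar time is described.

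Two further statements matter. The Eligibility criteria section requires unbroken insurance from January 2021 through December 2024 for everyone. The Descriptives section calculates standardized mean differences (SMDs) for all variables and regards values below 0.1 as good balance.

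**The concern.** In the target trial of Table 1, patients are randomized on the last day of the index event, so the arms are concurrent in expectation. In the emulation, concurrency holds only if the adjustment delivers it. With calendar time outside the score, a treated patient discharged in late 2023 can be matched to, or weighted against, a control discharged in early 2022. If readmission risk differed between those dates for reasons the listed covariates do not capture, the difference enters the treatment contrast. This applies to the 30-day primary outcome and to every 365-day secondary outcome, in both the intention-to-treat and the per-protocol analysis.

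The insurance rule adds a reason internal to the plan. A patient discharged in January 2022 must stay insured for about 35 more months to be included, and one discharged in December 2023 for about 12. Selection after discharge therefore differs by discharge date even without a secular trend. This alone does not bias the comparison, but it is one way in which risk in the analysed sample could depend on date.

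The planned diagnostics would miss the problem, because a balance table built on Table 2 has no row for calendar time.

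**Working it through.** **1. Benchmark from the plan's own sample size.** The Sample size calculation section gives effect size 0.3, 80% power, N = 449 at a 10% baseline and N = 329 at 20%. The metric, alpha and sidedness are not in the article, and its Appendix 1 is not shown. Assumed here: alpha 0.05 two-sided, 1:1 allocation, pooled-variance formula for two proportions without continuity correction, and 0.3 as a shift on the probit scale, p1 = Φ(z(p0) + 0.3).

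- p0 = 10%: p1 = 16.32%, difference 6.32 points, n = 449 per arm.
- p0 = 20%: p1 = 29.40%, difference 9.40 points, n = 329 per arm.

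Both stated figures are reproduced, as per-arm numbers and for an increase in readmission. The same 0.3 taken as a reduction gives 10% to 5.69% (4.31 points) and 20% to 12.68% (7.32 points). Calendar time is not an input, so the point does not touch the stated N.

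**2. Bias under no treatment effect.** Let Δr be the change in readmission risk from 2022 to 2023 not carried by the listed covariates. Let Δs be the difference between arms in the share of index events that fall in 2023.

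Bias on the risk-difference scale = Δr × Δs.

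The documents give neither quantity, so the values below are assumptions. Controls are split 50/50 between the years, and their average risk equals the baseline. Risk is taken to fall and the treated to be discharged later; reversing one of the two reverses the sign.

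| Δr (points) | Δs (points) | Bias (points) | Spurious OR, 10% baseline | Spurious OR, 20% baseline |
|---|---|---|---|---|
| 1 | 5 | 0.05 | 0.994 | 0.997 |
| 2 | 10 | 0.2 | 0.978 | 0.988 |
| 4 | 20 | 0.8 | 0.912 | 0.950 |
| 4 | 30 | 1.2 | 0.868 | 0.926 |
| 0 | any | 0 | 1 | 1 |
| any | 0 | 0 | 1 | 1 |

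Example, fourth row at 10%: control risk is 0.5 × 12% + 0.5 × 8% = 10.0%, and treated risk is 0.2 × 12% + 0.8 × 8% = 8.8%. The OR is (0.088/0.912)/(0.100/0.900) = 0.868.

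**3. Against the planned difference.** At a 10% baseline, 0.05/6.32 = 0.8% and 1.2/6.32 = 19%; against the reduction, 1.2/4.31 = 28%. At a 20% baseline, 1.2/9.40 = 13%; against the reduction, 1.2/7.32 = 16%.

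**4. Against sampling error.** With 449 per arm at 10%, the standard error of the risk difference is √(2 × 0.10 × 0.90/449) = 2.0 points, so 1.2 points is 0.6 standard errors. With 329 per arm at 20% it is √(2 × 0.20 × 0.80/329) = 3.1 points, so 1.2 points is about 0.4. In a larger sample the standard error shrinks and the bias does not.

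**5. What a balance row would show.** The SMD for a binary year indicator is Δs/√[(s1(1−s1) + s0(1−s0))/2]. For 55% against 50% in 2023 it is 0.05/0.499 = 0.10. For 80% against 50% it is 0.30/0.453 = 0.66. Even the smallest imbalance assumed above would reach the plan's own threshold of 0.1 if year were in the table.

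**The case against.** The case against has several parts.

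- *Bias needs two shifts.* A reader might infer that any change between 2022 and 2023 is read as a sociotherapy effect. That is wrong. The bias is a product, it vanishes if prescribing or readmission is flat, and it covers only what the listed covariates do not carry. This objection stands.
- *No trend is documented.* A reader might infer from the reform in the Background section that discharge prescribing was still growing. That section dates the reform to 2017, five years before the window opens, and the article reports no trend in prescribing or readmission. The direction of any bias is also unknown. This stands. An imbalance in dates does not need a prescribing trend, though. It would also arise if controls were indexed at their first event and treated patients at the prescribing event, a choice that the article does not spell out.
- *The size can be exaggerated.* Reading 0.3 as a 30% cut from 10% gives a 3-point benchmark and makes 1.2 points look like 40% of the effect. That reading does not reproduce 449 and 329. The differences that do are larger.
- *The emulation is not broken.* The target trial has no calendar blocking, and the Discussion already accepts unmeasured social confounders. One omitted covariate leaves conditional residual confounding and no more. This stands. But discharge date, unlike those social factors, is already held.
- *The article is condensed.* The adjustment set is nevertheless given variable by variable with diagnosis and procedure codes, and Assignment procedures points to Table 2 as the detailed description. The omission is therefore a feature of the set as fixed.

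**Conclusion.** The point holds as a conditional and probably modest risk. What the article establishes is that 24 months of discharges are pooled, that the listed adjustment set for both the propensity score and the outcome models has no calendar time, and that the balance check as planned could not reveal an imbalance in it. It also establishes that the insurance rule ties inclusion to discharge date.

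What it does not establish is that prescribing or readmission actually shifted, or in which direction. Under the assumed shifts the bias is about 0.05 to 1.2 percentage points. At a 10% baseline that is roughly 1% to 19% of the planned difference, or up to 28% if that difference is taken as a reduction. These ratios rest on an inferred effect-size metric. The article does not support a claim that the primary result would be invalid. It does support closing the gap before the propensity model is fitted.

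**What to change.** Add calendar time of discharge to Table 2, so that it enters three places: the propensity score, the outcome models and the SMD balance table. Year is the minimum. Quarter (eight levels) also covers seasonal variation and should be used if the number of treated patients allows. Exact matching within quarter is optional in the matching branch, and nothing in the article makes it necessary.

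Year costs one parameter and quarter seven, in a score that already has many covariates and with a number of treated patients not yet known. The discharge date is already needed to set the start of follow-up, and the stated N is unchanged. If calendar time predicts prescribing but not readmission, adding it loses a little precision and could slightly amplify other residual confounding. Reporting the primary result with and without the term would show whether that matters. A year term removes the between-year component of the bias and leaves variation within years; quarter removes most of that as well.

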### Follow-up period

We follow up with participants for 30 days after discharge to assess the primary outcome, and for up to 365 days for secondary outcomes, or until death—whichever occurs first. During the follow-up period, we will evaluate the continuation of sociotherapy prescriptions as a component of a structured DM, as well as any new prescriptions issued in the outpatient setting.

### Outcomes

The primary outcome is the average treatment effect among the treated (ATT) on the 30-day readmission rate to a psychiatric hospital. A readmission is defined as a subsequent admission to an inpatient setting for patients who were previously discharged from an inpatient setting. For patients who received the index treatment in an inpatient-equivalent setting, a readmission includes admission to inpatient, or inpatient-equivalent setting. For patients who received the index treatment in a semi-inpatient setting, a readmission includes admission to any of these levels of care: inpatient, semi-inpatient, or inpatient-equivalent. However, a transfer between these settings is not considered a readmission but rather a continuation of the index event, provided that the transfer occurs on the same day. In addition to the primary outcome, we define the following secondary outcomes: the ATT on 365-day readmission rate for psychiatric hospitalization, the ATT on time to first psychiatric readmission, the ATT on total number of psychiatric hospitalizations within a 365-day period, and the cumulative number of days spent in the hospital due to psychiatric admissions during this time frame.

### Statistical analysis

#### Descriptives

Descriptive statistics will be used to summarize the baseline characteristics of participants prior to and after PSM. Continuous variables will be reported as means with standard deviations or medians with interquartile ranges, depending on their distribution, while categorical variables will be presented as frequencies and percentages. To assess baseline balance between the groups after PSM, the Standardized Mean Difference (SMD) will be calculated for all variables, with a SMD of less than 0.1 indicating a good balance.

#### Intention-to-Treat Analysis (ITT)

All patients assigned to the study population within the PSMprocedure will be included in the ITT. Patients will be analyzed according to the group to which they were assigned.

#### Per-Protocol Analysis (PPA)

The per-protocol population will include only those patients who were assigned to the study population within the PSM procedure and adhere to the study protocol. For the intervention group adherence will be defined as the utilization of least one sociotherapy session prescribed as a DM measure. For the control group adherence will be defined as standard care. However, sociotherapy sessions prescribed in any other setting will be defined as a violation of the protocol for this group.

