Follow-Up Period	Starts at randomization and ends 30 days/365 days after discharge of the index event, death, or loss to follow-up	Starts at the last day of the index event and ends 30 days/365 days after discharge of the index event, death, or loss to follow-up
Outcome	Primary outcome • Readmission to hospital for psychiatric treatment within 30 days after discharge Secondary outcomes • Readmission to hospital for psychiatric treatment within 365 days after discharge • Time to first psychiatric rehospitalization • Total number of rehospitalizations within 365 days after discharge • Cumulative number of days spent in the hospital due to psychiatric admissions during 365 days after discharge	Primary outcome • Readmission to hospital for psychiatric treatment within 30 days after discharge Secondary outcomes • Readmission to hospital for psychiatric treatment within 365 days after discharge • Time to first psychiatric rehospitalization • Total number of rehospitalizations within 365 days after discharge • Cumulative number of days spent in the hospital due to psychiatric admissions during 365 days after discharge
Causal Contrasts Of Interest	• Intention-To-Treat (ITT): The ITT evaluates the average treatment effect among the treated (ATT), regardless of whether the patients adhered to the treatment • Per-Protocol (PPA): The PPA evaluates the average treatment effect among the treated (ATT), accounting for the non-adherence to the sociotherapy treatment in the intervention group, and usage of sociotherapy in the control group due to prescriptions of sociotherapy unrelated to the assignment procedure	• Intention-To-Treat (ITT): The ITT evaluates the average treatment effect among the treated (ATT), regardless of whether the patients adhered to the treatment • Per-Protocol (PPA): The PPA evaluates the average treatment effect among the treated (ATT), accounting for the non-adherence to the sociotherapy treatment in the intervention group, and usage of sociotherapy in the control group due to prescriptions of sociotherapy unrelated to the assignment procedure

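### The per-protocol analysis selects patients on a session used after discharge while counting events from discharge, so its 30-day result leans towards benefit even when there is no effect

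*Protocol article*

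**What the plan says.** - **Time zero.** Table 1 (Design) sets the emulation's follow-up as: "Starts at the last day of the index event and ends 30 days/365 days after discharge of the index event, death, or loss to follow-up".
- **Who is kept.** Per-Protocol Analysis: "The per-protocol population will include only those patients who were assigned to the study population within the PSM procedure and adhere to the study protocol". Among prescribed patients the criterion is attendance after discharge: "adherence will be defined as the utilization of least one sociotherapy session prescribed as a DM measure". For controls, "sociotherapy sessions prescribed in any other setting will be defined as a violation of the protocol for this group".
- **Exposure.** Table 2 (Confounders) gives the per-protocol exposure as "Prescription of Sociotherapy as a DM and utilization of at least one sociotherapy session (PPA"), a fixed yes/no variable.
- **Model.** Analyses of primary and secondary outcomes: "Both ITT and PPA will use the same statistical models for the analysis". The adjustment set in Confounders and Table 2 covers the index event, other DM measures, medical history and sociodemographics. Nothing in it is measured after discharge.
- **Scope and use.** "Both ITT and PPA will be applied to all secondary outcomes". When ITT and per-protocol results are set side by side, "we can only compare whether the effects are positive or negative".
- **Timing.** Background limits DM measures to seven days after discharge and says sociotherapy should ideally start at once. No distribution of first-session dates is given.

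**The concern.** Attending a session happens after time zero, and a patient normally has to be still out of hospital to do it. Retained intervention patients are therefore event-free up to their first session by construction (immortal time), whereas retained controls are at risk, with events counted, from day 0. Covariates fixed at discharge cannot correct a selection made on what happens afterwards.

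Table 1 presents the per-protocol effect as an ATT that accounts for non-adherence, but the only mechanism stated is exclusion. This is a stated rule that gives a biased answer, not a detail that an article would normally leave to a fuller plan.

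The per-protocol effect is one of only two causal contrasts named, and it is applied to every outcome. Because the two contrasts are to be compared by sign alone, a bias that supplies a protective sign under no effect acts directly on the planned interpretation.

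**Working it through.** The article states no figure for the per-protocol analysis, so there is none to reproduce. Its sample sizes are used in step 5 only.

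**1. Inputs.** From the article: baseline 30-day risks r of 10% and 20% (Sample size calculation), follow-up from discharge (Table 1), the seven-day DM limit (Background). Assumed: no true effect, a constant daily readmission hazard L, first session uniform over days 0 to G, attendance unrelated to prognosis, and no qualifying session after a readmission.

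**2. Formula.** L = −ln(1 − r)/30. A prescribed patient is kept only if the session day S comes before the readmission day T, and P(S < T) = (1 − e^(−LG))/(LG). The 30-day risk among those kept is therefore

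1 − (1 − r) × f, with f = LG/(1 − e^(−LG)).

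**3. Seven-day period, flat hazard (G = 7).**

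| | r = 10% | r = 20% |
|---|---|---|
| L per day | 0.003512 | 0.007438 |
| LG | 0.02458 | 0.05207 |
| f | 0.02458/0.02428 = 1.0123 | 0.05207/0.05073 = 1.0263 |
| Risk among those kept | 1 − 0.9 × 1.0123 = 8.9% | 1 − 0.8 × 1.0263 = 17.9% |
| Risk ratio | 0.89 | 0.89 |
| Odds ratio | 0.88 | 0.87 |

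A null simulation with 4 million patients per arm (60% attendance and 5% control crossover over a year, both assumed) gave 8.88% and 17.90% in the retained intervention group, with odds ratios of 0.875 and 0.867.

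**4. Sensitivity to the assumptions.**
- Sessions over days 0–3: f = 1.0053 at 10%, so the risk is 1 − 0.9 × 1.0053 = 9.5% and the risk ratio is about 0.95. At 20%, f = 1.0112, the risk is 19.1% and the risk ratio is 0.96.
- First-week hazard k times the later hazard, 30-day risk held at 10%, G = 7: the first-week cumulative hazard is −ln(0.9) × 7k/(7k + 23). For k = 2 this is 0.0399, f = 1.0201, risk 8.2%, risk ratio 0.82. For k = 3 it is 0.0503, f = 1.0254, risk 7.7%, risk ratio 0.77. The article gives no source for k.
- 365 days, G = 7, same hazard carried forward: at 10%, 1 − e^(−365L) = 72.2% against 71.9%, odds ratio 0.98; at 20%, 93.4% against 93.2%, odds ratio 0.97.

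**5. Chance of a significant false benefit (nominal 2.5%), G = 7.** The stated 449 (10% baseline) and 329 (20%) reproduce as per-arm numbers at two-sided 5% and 80% power if 0.3 is a probit-scale shift (10.0% against 16.3%; 20.0% against 29.4%). With those numbers retained per arm, the chance is 8% and 10%. With about half retained (225 and 165 per arm), it is 6% and 7%.

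**6. Control exclusions.** Let q be the share of readmitted controls excluded and q0 the share of the non-readmitted excluded. The control odds are multiplied by (1 − q)/(1 − q0). If sociotherapy tends to follow a readmission (q > q0), control risk falls and the bias works against sociotherapy. If it tends to start while patients are out of hospital (q < q0), control risk rises and the bias favours sociotherapy. The article gives neither q nor q0. In the 365-day null simulation, dropping controls whose sociotherapy followed a readmission could move the odds ratio to about 0.99–1.09.

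**7. Does aligning follow-up remove the bias?** In the same null simulation with G = 7, counting grace-period events for all prescribed patients and censoring controls at crossover gave odds ratios of 0.998 (10%) and 0.997 (20%). A day-7 landmark gave the same values.

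**The case against.** The strongest reply is that the problem is modest and confined to the per-protocol contrast. The ITT is fixed by prescription at time zero and is untouched. Only DM-prescribed sessions qualify and DM measures end at day seven, so the immortal period is short; if sessions start promptly, the risk ratio is about 0.95. At 365 days the effect is slight. Restriction to attenders also leaves fewer patients, and so less chance of declaring the spurious benefit significant. All of this stands and limits the size, but it does not remove the bias or its direction in the intervention group.

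Because no session window is stated, a session used after an early readmission might still count. The seven-day limit leaves little room for that.

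A reader might infer more than the article supports:
- **Much larger bias from late first sessions.** Spreading them over 14 or 30 days gives odds ratios near 0.75 or 0.49, but this conflicts with the seven-day limit. The Conclusion's remark about slow provision names a possible barrier to explore and gives no timing.
- **An offsetting bias from the control exclusions.** Step 6 shows that the direction is not fixed. It is also unclear whether sociotherapy prescribed at a later discharge counts as prescribed in another setting; the wording in Table 1 is broader.
- **Harm from broken matched pairs.** Matching or weighting is left open and no pair-conditional analysis is stated, so nothing in the article depends on intact pairs.

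**Conclusion.** The concern holds for the per-protocol analysis. As written, it is biased towards benefit at 30 days through the intervention group. Under no effect, a flat hazard and first sessions uniform over the seven-day DM period, the odds ratio is about 0.88 at 10% baseline risk and 0.87 at 20%. It moves towards 1 with earlier sessions and away from 1 if the first-week hazard is raised. Session timing is an assumption throughout, and attendance related to prognosis would add selection not quantified here. The control exclusions are a second outcome-dependent selection of indeterminate direction.

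This is a moderate bias in one of two contrasts and no reason to doubt the ITT. It still matters, because agreement in sign between the two contrasts would partly be produced by the design.

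**What to change.** Replace exclusion with a per-protocol analysis that follows everyone from discharge in the arm set by prescription:

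1. Use a seven-day grace period, taken from the plan's own DM limit.
2. Count readmissions inside the grace period for all prescribed patients, whether or not a session took place.
3. Censor prescribed patients without a session at the end of the grace period, and controls at first sociotherapy use from any source. Reconcile the control-violation wording with Table 1.
4. Apply inverse-probability-of-censoring weights, from baseline covariates and whatever post-discharge claims covariates are available, together with the propensity-score step so that the ATT remains the target.
5. Amend the sentence that gives ITT and per-protocol the same models, and the per-protocol exposure row in Table 2.

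Cloning is not needed, because prescription already separates the two strategies at time zero. A day-7 landmark analysis can serve as a sensitivity check, with a note that it discards first-week readmissions and so changes the estimand.

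The cost is extra programming on claims data, which must carry session dates, and somewhat wider intervals from the weighting. Table 2 currently lists no post-discharge covariates, so these would have to be defined.
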